*Overtreatment (inappropriately intensive glycemic control) is common.* We have developed a measure of "potential over-treatment" operationally defined as: A1c < specific threshold (<7%, <6.5%, or <6%) representing increasingly intensive glycemic control, treatment with insulin and/or sulfonylurea, and one of the following: (a) >75 years of age, (b) serum creatinine >2 mg/dl, or (c) cognitive impairment or dementia. Our study indicates that up to 50% of patients in VA meeting these criteria are potentially being overtreated. Moreover, there is evidence of considerable facility-level variation: Rates of overtreatment ranged from 6.1 to 23.0%, 20.4 to 45.9%, and 39.7 to 65.0% for A1c thresholds of <6%, <6.5%, and <7%, respectively. These measures are less "sensitive" than the American Geriatrics Association recommendation for the *Choosing Wisely Campaign*, which is, "Avoid using medications to achieve hemoglobin A1c <7.5% in most adults age 65 and older." After excluding A1c <7% in the < 65 year old population and other conditions recommended by VA/DoD guidelines, ~65% receiving hypoglycemic agents would be considered at high risk for serious hypoglycemia. Tackling such a problem presents challenges at multiple levels of the healthcare system.

*Many factors have contributed to the frequency and persistence of overtreatment.* For more than 15 years the American Diabetes Association (ADA) guidelines have supported a target A1c of <7% for "most" adults aged 18-75. Similarly, performance measures reflect perspectives of different stakeholders, but form an important part of the organizational context of healthcare. The National Committee for Quality Assurance's Healthcare Effectiveness Data and Information Set (NCQA-HEDIS®)'s A1c <7% measure for all patients aged 18-74 years was introduced in 2006 despite the unanimous opposition of the National Quality Improvement Alliance's Technical Advisory Panel. New measures were introduced only after the premature termination of the ACCORD trial. Nevertheless, current measures now include <7% measure for persons less than 65 years of age without advanced diabetes complications, cardiovascular or ischemic disease, or dementia; and <8% measure was introduced for all other persons 18-75 years of age. We note that VHA did NOT endorse any of these measures, including the <8% measure, because of concern over hypoglycemia.

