differences in probability of overtreatment (e.g., A1c <6.5%) rates for facility-level predictors in a two-level model. We note that in 2009, there were ~205,000 with insulin/sulfonylurea who were  $\geq 75$  years old, or with either diagnosis of dementia or cognitive impairment, or having serum creatinine >2.0 mg/dl from at least 130 VA medical centers across the nation. We also estimated that the number of such high risk patients in each facility range from 300 to 7,000. Based on 2009 data on the high risk patients, 28.6% (facility variation: 24.7%-32.7%) had their last A1c values < 6.5%. Since 2009, the number of patients has increased. We assumed a

[figure not shown]

“control/reference” group probability of overtreatment of 0.290 based on our data from 2009. We assumed a Type I error rate of 0.05 for two-sided tests. We conducted power analysis based on 130 facilities and 300 (or 150) patients per facility. Figure 3 shows the relationship between power achieved and the overtreatment probability for the treatment group ( $P(TX)$ ). The graph shows that when  $P(TX)$  moves away from 0.29 (namely, the group contrast becomes larger) and  $n$  is bigger, power increases. For example, we will have more than 0.8 power if  $P(TX) \leq 0.273$  (detectable minimum group difference ( $d$ ) = 0.017) for  $n=300$  and  $P(TX) \leq 0.268$  for  $n=150$  ( $d=0.022$ ). Our power calculations are based on 130 facilities with either 300 or 150 patients each and thus are extremely conservative and indicate that there will be sufficient power for subgroup analyses. The power calculation also has to consider the dependence among observations nested within the same cluster. However, we note that intraclass correlation for binary outcomes is less

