## 2.4.5. Dependent and Independent Variables (Quantitative)

### 2.4.5.1. Dependent Variables (Outcome Measures for Summative Evaluation)

**Overtreatment and undertreatment.** Using the last A1c value in a time period we will define overtreatment if it is less than the thresholds of 6.5% (we will evaluate 6.0% and 7.0% for sensitivity analysis). If the same A1c value is greater than 9.0%, it is considered undertreatment. Those in the range of 6.5% to 9.0% are considered to be in moderate glycemic control and will be used as the reference group in statistical analyses.

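### Section 2.4.4 and the Background give facility spreads of 8.0 and 25.5 points at A1c <6.5% without reconciling them; the stated power fits the narrow one and, unadjusted, not the wide one

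*Protocol*

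**What the plan says.** Section 2.4.5.1 sets the main threshold: "we will define overtreatment if it is less than the thresholds of 6.5"%. Two places give the spread of facility rates at that threshold.

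- **Section 2.1 (Background):** "Rates of overtreatment ranged from 6.1 to 23.0%, 20.4 to 45.9%, and 39.7 to 65.0% for A1c thresholds of <6%, <6.5%, and <7%, respectively". The text introduces this by saying "there is evidence of considerable facility-level variation". No year is given. The group is patients on insulin and/or a sulfonylurea who are over 75, have creatinine above 2 mg/dl, or have cognitive impairment or dementia.
- **Section 2.4.4 (Power Analysis):** "28.6% (facility variation: 24.7%-32.7%) had their last A1c values < 6.5"%. This is for 2009, in essentially the same high-risk group (age is 75 or over here). The statistic behind the interval is not named.

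The power calculation takes a control "group probability of overtreatment of 0.290 based on our data from 2009" and states "We assumed a Type I error rate of 0.05 for two-sided tests". It uses 130 facilities with 300 or 150 patients each and concludes "we will have more than 0.8 power if" the comparison rate is at most 0.273 (n=300, difference 0.017) or 0.268 (n=150, difference 0.022). The section describes this as strongly conservative, and adds that the approach copes even with large intraclass correlations. It gives neither an intraclass correlation nor a between-facility variance.

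**The concern.** Participation in the initiative is a facility-level exposure. In a two-level comparison the between-facility variance therefore sets a floor on precision that more patients per facility cannot lower. One spread is 32.7 − 24.7 = 8.0 points wide and the other is 45.9 − 20.4 = 25.5 points wide, for the same threshold and nearly the same patients. The change from over 75 to 75 and over is not offered as the reason and seems too small to triple a spread.

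At stake are the detectable differences of 0.017 and 0.022 for H1.1, the statement that subgroup analyses are adequately powered, and the assurance about intraclass correlation. All of these depend on which spread describes the facilities.

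**Working it through.** **Inputs from the protocol.** Control rate 0.290; comparison rates 0.273 (n=300) and 0.268 (n=150); 130 facilities; two-sided 0.05; the two spreads. **Assumption.** 65 facilities per group, since the power section states no split.

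**Method.** On the logit scale, τ = [logit(upper) − logit(lower)]/k. Here k = 3.92 if the spread is a 95% interval, 5.2 if it is the full range of about 130 normal values (the expected range), and 6 as a further reading. Then SE² = (τ² + 1/(n·p₁q₁))/65 + (τ² + 1/(n·p₀q₀))/65, with 128 df.

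The logit differences are 0.0841 (0.290 v 0.273) and 0.1094 (0.290 v 0.268). The sampling terms are 0.0168 and 0.0162 at n=300, and 0.0340 and 0.0324 at n=150.

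**1. The plan's own figure.** Narrow spread: 0.393/3.92 = 0.100, so τ² = 0.0100.
- n=300: SE = √[(0.0268 + 0.0262)/65] = 0.0286; 0.0841/0.0286 = 2.94; power 0.83.
- n=150: SE = 0.0365; 0.1094/0.0365 = 3.00; power 0.85.
- Differences detectable with 0.8 power: 0.0163 and 0.0207, against the stated 0.017 and 0.022.
- Reading the narrow spread as a full range gives 0.89 to 0.91 at n=300. No clustering at all gives 0.96 and 0.92.

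The stated figures therefore imply a small facility variance, of about the size the narrow spread gives.

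**2. The Background range instead.** The logit width is 1.197.

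| Reading | τ² | Power at 0.017, n=300 | Power at 0.022, n=150 | Detectable difference, n=300 |
|---|---|---|---|---|
| 95% interval (k=3.92) | 0.093 | 0.30 | 0.41 | 0.033 |
| Full range of 130 (k=5.2) | 0.053 | 0.44 | 0.56 | 0.026 |
| 6 SD | 0.040 | 0.52 | 0.63 | 0.024 |

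**3. Sensitivity.**
- *Skewness.* The range runs 8.2 points below 28.6% and 17.3 above, so a few high facilities may drive it. Using the lower tail only, SD ≈ 8.2/2.6 ≈ 3.1 points. On the probability scale this gives power of about 0.66 to 0.67 at n=300.
- *Sampling error.* Observed rates include it. Netting it out gives 0.46 (k=5.2, about 1,580 patients per facility) and at most 0.66 (6 SD, every facility taken at n=300).
- *Larger facilities.* The mean is about 205,000/130 ≈ 1,580. Power at 0.017 is then 0.33, 0.52 and 0.63 for the three readings. With the lower-tail SD it is about 0.83.
- *Uneven split.* With 20 to 30 focus facilities (4–6 VISNs of about 5, section 2.4.2), power at n=300 is 0.56 to 0.69 even with the narrow spread.

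**4. The intraclass correlation assurance.** On the latent scale ICC = τ²/(τ² + 3.29). The narrow spread gives 0.003 and the wide one 0.012 to 0.028. At n=300 and a 1.7-point difference, an ICC of 0.02 gives power 0.38 and 0.05 gives 0.19.

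**The case against.** **The two ranges may be different summaries.** A reader might infer that both cannot be true. The protocol does not support that, because section 2.4.4 names no statistic. If 8.0 points were an interquartile range, the SD would be 8.0/1.349 = 5.9 points, and a full range of 25.5 points across 130 facilities would be compatible with it. This stands against calling either figure false. It does not rescue the power, which under that SD is about 0.32 at n=300.

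**The software input is inferred.** The protocol does not say that 24.7%–32.7% was entered, and the power figure is not shown. This stands. The link rests on reproduction and on the assumed even split.

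**The planned model adjusts for baseline.** Section 2.4.8 includes each patient's pre-initiation glycemic status, so residual variance is what counts. This is the strongest point. Section 2.4.4 gives an SD of 2.4 for year-to-year facility change at A1c <6%, where section 2.1 gives a range of 6.1–23.0%. With SD = 16.9/5.2 = 3.25, r = 1 − 2.4²/(2 × 3.25²) = 0.73 and r² = 0.53. If that stability carries over to <6.5% and patient-level adjustment acts like facility-level adjustment, τ² falls from 0.053 to 0.025. Power is then 0.65 at n=300 and 0.81 at 1,580 patients (0.79 to 0.83 at 1,580 across the three readings of the ranges). So adjustment could restore about 0.8 at average sizes. At n=300 it would have to remove about 69 to 87% of the facility variance, and the power section claims no such credit.

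**The practical consequence is limited.** Power sets no sample size here, since section 2.4.2 takes in all VA facilities above a minimum number of Veterans with diabetes. For a 4.6-point difference, the lower end of the VISN 12 falls cited in section 2.4.4, unadjusted power with the wide spread is at least 0.98 at n=300 with an even split. A reader might also infer that a null result will be reported as no impact. The protocol does not say so: it reports odds ratios with confidence intervals and promises cautious causal inference.

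**Conclusion.** The point holds as an unreconciled input and a detectable difference that the document does not support as stated. The plan's figures match the narrow spread. With the Background range, unadjusted power at 1.7 points and n=300 is about 0.3 to 0.5, up to about 0.67 on the lower-tail or sampling-error readings. The difference detectable with 0.8 power is about 2.4 to 3.3 points.

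This rests on an even split, on the Background range describing about 130 facilities, and on how that range is converted to an SD. It does not show that the planned adjusted analysis is underpowered. A reader might infer a single corrected power of 0.4 to 0.5, but that is one reading within a wider range and ignores adjustment. What fails at the protocol's own 300 patients per facility is the description of the calculation as conservative and the assurance about large intraclass correlations. Taking fewer patients per facility is conservative at the patient level, whereas the limiting variance lies between facilities.

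**What to change.** 1. In sections 2.1 and 2.4.4, say what each range describes: unit, year, number of facilities, and whether it is a full range, an interval or a quartile range.
2. State the between-facility variance, estimated from the 2009 facility rates net of sampling error, and the assumed split of facilities.
3. Rerun the two-level calculation with that variance. If credit is taken for pre-initiation glycemic status, state the proportion of facility variance it is assumed to remove and show the result without it.
4. Replace the differences of 0.017 and 0.022 with the results. Remove or qualify the claims that the calculation is conservative and copes with large intraclass correlations, and recheck the statement on subgroup power.

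The cost is one rerun on data already held and a wording change. The stated detectable difference is likely to become less favourable. The study's size, data collection and analysis model need not change.

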For Aim 1 we will use a hierarchical ordinal logistic regression approach using patient-level longitudinal data (4/1/14 to 3/31/2015) to model the probability of overtreatment (and undertreatment) in which Choosing Wisely Initiative participation status (focus on overtreatment of diabetes, overuse of MRI for low back pain, both, or neither) is the key predictor variable of interest. Using patient-level data will provide power to identify even modest differences between groups. Aim 2 will utilize similar methods to assess associations with the facility characteristics of commitment to quality, teaching intensity, and safety culture. Aim 3 will utilize facility-level (cross-sectional) aggregate data (4/1/13 to 3/31/2016). High and low performers will be identified based on changes in overtreatment rates pre- and post-initiative (rather than on absolute values). In order to minimize issues related to regression to the mean as well as floor and ceiling effects, we will focus on facilities that were mid-performing at baseline (2nd and 3rd quartiles). We will focus on those facilities which had high reductions in overtreatment rates at 12 months (high performers) and those who had low (or negative) reductions in overtreatment rates, i.e., got worse, (low performers). Surveys and phone interviews will be conducted to assess what practices were (or were not) implemented to reduce overtreatment, as well as what barriers and facilitators existed to following the initiative. (DM-QUERI has committed funds to support pre-funding work, including instrument refinement and testing - see support letter). Field testing will continue in year 1. The purpose of the surveys of high and low performing sites is to provide the data for the qualitative comparative analysis (QCA) to assess which factors contribute to the difference in performance. Data from semi-structured interviews and site visits will enhance the interpretation. At year 2, the findings of the QCA will be assessed in depth via site visits to the high performing sites, with artifact collection, procedural observation, and in person semi-structured interviews conducted with clinicians (including CPSs, PCPs, and clinic managers), to enhance understanding of contextual factors. Our overall approach is based on the methods developed and used by the

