straightforward than for continuous outcomes. In fact, Spybrook and Raudenbush who developed the Optimal Design software stated: “In the case of a binary outcome, we do not typically standardize the model because the level-1 variance is heteroskedastic, which makes the meaning of the intraclass correlation,  $\rho$ , uninformative.” Our conservative approach will accommodate even large intraclass correlations. Aim 3’s selection of high and low performers is based on changes in facility-level overtreatment rates. We cannot be certain which facilities will choose to focus on hypoglycemia risk reduction as opposed to another Choosing Wisely topic area or none at all. Previous experience (courtesy of National Program Director for Medicine) suggests that a minimum of 4-6 VISNs will choose the hypoglycemia risk reduction focus, each with an average of 5 facilities. In addition, sites in other VISNs may implement this intervention. We obtained data from 2009 and 2010 to assess year to year variation. This allowed us to estimate power based on a paired  $t$  test for a simple pre-test post-test design. One hundred random samples of 20 facilities were chosen. The mean  $\pm 1$ SD change in overtreatment rate for the A1c <6% threshold, a level that puts patients at the highest risk was an absolute percent reduction of  $-0.9 \pm 2.4$ , e.g., an overtreatment rate falling from 10% to 9.1%. Based on paired  $t$  test, our study will require as few as 15 facilities to detect an absolute overtreatment rate reduction of 2.9, e.g., 10% to 7.1%, with 85% power, even assuming as little as 50% correlation between the SDs of each of the two measurements. This compares favorably with preliminary work from VISN 12 which showed that rates of overtreatment fell by 4.6 to 5.9 at the three A1c thresholds.

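### The power section claims tolerance of large intraclass correlations, but its only reserve is patients per facility, which cannot offset between-facility variance; 80% power at 1.7 points is lost above an ICC of about 0.006 at any number of patients

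*Protocol*

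**What the plan says.** Section 2.4.4 (Power Analysis) describes a two-level model for facility-level predictors of overtreatment at A1c <6.5%. Its inputs are: "We assumed a Type I error rate of 0.05 for two-sided tests"; a reference "group probability of overtreatment of 0.290 based on our data from 2009"; and "We conducted power analysis based on 130 facilities and 300 (or 150) patients per facility". For 300 patients per facility it says "we will have more than 0.8 power if" the treated-group probability is 0.273 or lower ("detectable minimum group difference ( $d$ ) = 0.017"). For 150 patients the figure is 0.268, a difference of 0.022.

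The same section puts the real number of high-risk patients at 300 to 7,000 per facility. It says the calculations are "thus are extremely conservative and indicate that there will be sufficient power for subgroup analyses". It then acknowledges that dependence within clusters has to be considered, states no ICC, cites the software manual to the effect that the ICC is uninformative for binary outcomes, and ends with "Our conservative approach will accommodate even large intraclass correlations".

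Section 2.4 (Overview) makes a related but general remark: "Using patient-level data will provide power to identify even modest differences between groups".

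The protocol gives facility variation at A1c <6.5% twice: 20.4% to 45.9% in section 2.1, and 24.7% to 32.7% around an overall 28.6% in section 2.4.4. Section 2.1 places the choice of initiative at VISN or facility level. Section 2.4.5.2 defines commitment to quality, teaching intensity and safety culture as facility measures.

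**The concern.** The calculation is conservative only in assuming fewer patients per facility than there are. The number of facilities is not held back: 130 is used, and the text cites at least 130. When the exposure is constant within a facility, extra patients shrink only the within-facility part of the variance. The between-facility part is divided by the number of facilities alone. A reserve of patients therefore protects against a small ICC but not a large one.

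What is at stake is how results are read. H1.2 expects the same likelihood of undertreatment, and H1.1 and H2.1a to H2.1c all concern facility-level exposures. A reader who accepts the tolerance claim would take a null result as more informative than it may be. The same applies to subgroups, where patients per facility fall while the between-facility part stays.

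**Working it through.** **Inputs.** From section 2.4.4: two-sided 0.05; p0 = 0.290; p1 = 0.273 (n = 300) or 0.268 (n = 150); 130 facilities. Average facility size is 205,000/130, or about 1,577. The split between groups is not stated for this calculation, so 65 v 65 is assumed.

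**Formulas.** With τ the between-facility SD of the overtreatment proportion:

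- SE² = [τ² + p1(1−p1)/n]/J1 + [τ² + p0(1−p0)/n]/J0
- power = Φ(d/SE − 1.96)
- ICC = τ²/[p(1−p)], where p(1−p) = 0.29 × 0.71 = 0.2059
- difference detectable with 80% power = 2.80 × SE

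**1. Reproducing the plan's figure.** Read 24.7% to 32.7% as a 95% interval: τ = 0.080/3.92 = 0.0204, τ² = 0.000416, ICC = 0.002.

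- n = 300: SE² = (0.000416 + 0.000662)/65 + (0.000416 + 0.000686)/65, so SE = 0.00579. Power = Φ(0.017/0.00579 − 1.96) = 0.835.
- n = 150: SE = 0.00735. Power = Φ(0.022/0.00735 − 1.96) = 0.849.

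Both match the stated power of more than 0.8. With no clustering the powers would be 0.96 and 0.93, so the stated minimum differences fit a calculation with a small ICC, not one that ignores clustering.

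**2. The limit that patients cannot move.** As n grows without bound, SE tends to τ × √(4/130) = 0.1754τ. For 80% power at 1.7 points, SE must be at most 0.017/2.80 = 0.00607, so τ must be at most about 3.5 points, an ICC of about 0.006. The largest ICC that keeps 80% power at 1.7 points is:

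| Patients per facility | Largest ICC |
|---|---|
| 300 | 0.0026 |
| 1,577 | 0.0053 |
| unlimited | 0.0059 |

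**3. The other spread in the protocol.** For 20.4% to 45.9% (section 2.1):

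- as the full range of 130 facilities (about 5.2 SDs for normal values): τ = 0.255/5.2 = 0.049, ICC 0.012
- as a 95% interval: τ = 0.255/3.92 = 0.0651, ICC 0.021

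Power at 1.7 points (normal approximation, then noncentral t on 128 df) and detectable difference, 65 v 65:

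| Between-facility SD | Power, n = 300 | Power, unlimited n | Detectable, n = 300 | Detectable, unlimited n |
|---|---|---|---|---|
| 2.0 points | 0.835 / 0.830 | 0.997 / 0.997 | 1.6 points | 1.0 points |
| 4.9 points | 0.416 / 0.410 | 0.507 / 0.501 | 2.7 points | 2.4 points |
| 6.5 points | 0.282 / 0.279 | 0.319 / 0.315 | 3.4 points | 3.2 points |

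**4. Unequal split.** Section 2.4.4 expects at least 4 to 6 VISNs of about 5 facilities to choose the hypoglycemia focus, that is 20 to 30 facilities. With 25 v 105, ICC 0.002 and n = 300, SE = 0.0073 and power at 1.7 points is 0.64.

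**5. Subgroups.** A subgroup of 10% to 20% of an average facility has about 158 to 315 patients, roughly the sizes the plan powered. At an SD of 2.0 points the stated differences of 1.7 to 2.2 points therefore hold. At SDs of 4.9 and 6.5 points and n = 150, the detectable difference is 3.0 and 3.7 points.

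**The case against.** - **The larger ICC is an upper reading.** The range in section 2.1 is observed and unadjusted, so it includes sampling error. This stands as a caveat. Removing sampling variance at the average facility size (0.2059/1,577 = 0.00013, or 0.0006 on the ICC scale) leaves about 0.011 to 0.020. Smaller facilities would contribute more noise.
- **At the spread printed in the power section, the patient reserve works.** This stands: at ICC 0.002, power at 1.7 points rises from 0.84 with 300 patients to 0.99 with 1,577. But that is tolerance of a small ICC.
- **Adjustment for pre-initiative glycemic status (section 2.4.8) may shrink the between-facility variance.** It may. Starting from ICC 0.02 with unlimited patients, removing 50% gives power 0.58 and removing 75% gives 0.86. The power section claims no such reduction.
- **1.7 points is a minimum detectable difference, not an expected effect.** The protocol cites falls of 4.6 to 5.9 points in VISN 12. For 4.6 points at ICC 0.02, n = 300 and 65 v 65: SE² = (0.02 + 0.98/300) × (0.2059 + 0.1845)/65, SE = 0.0118, and power = Φ(0.046/0.0118 − 1.96) = 0.97. That figure is a change over time, not a contrast between groups, but it shows that larger effects could survive a moderate ICC.
- **Other safeguards.** The protocol reports confidence intervals, plans facility and VISN random effects, promises cautious causal inference, and names too few participating facilities as a risk. These soften the consequences but do not make the sentence true.

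A reader might infer that the power calculation ignored clustering, that the study as a whole is underpowered, or that the subgroup statement is simply false. The documents support none of these. The stated power reproduces with a small ICC, no target effect is fixed at 1.7 points, and subgroups of about 150 to 300 patients per facility keep the stated differences at the smaller spread. The general remark in section 2.4 gives no size or ICC and is not a separate error.

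**Conclusion.** The claim of tolerance for large ICCs is wrong as written. The stated power depends on a between-facility SD of about 2 points. At 1.7 points, 80% power is lost above an ICC of about 0.0026 with 300 patients per facility and about 0.006 with any number.

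This matters on the protocol's own figures, because its two facility spreads for the same threshold lead to different answers. One gives power of about 0.84 with 300 patients per facility; the other gives about 0.41 to 0.28.

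These results assume a 65:65 split, the stated readings of the two spreads, no variance removed by covariates, and no VISN-level clustering. An unequal split or choice at VISN level would lower power; effective baseline adjustment would raise it. The point is a correction to a claim about power. It does not question the sample or the analysis model.

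**What to change.** In section 2.4.4:

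1. Delete the sentence on large intraclass correlations, and say that power for facility-level exposures is limited by the number of facilities and the spread between them.
2. Reconcile the facility spreads in sections 2.1 and 2.4.4, stating what each one is (full range, 95% interval or other) and whether it is adjusted.
3. Add a small table of detectable differences for between-facility SDs of about 2 to 6.5 points at the actual number of facilities. Include an unequal split such as 25 v 105, and note that adjustment for pre-initiative glycemic status may reduce the variance.
4. Limit the subgroup power statement to the conditions under which it holds: about 150 to 300 patients per facility at an SD of about 2 points.

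The cost is a few sentences and one table. No data, sites or analyses are added. The stated precision becomes less favourable at the larger spreads.
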